**Exclusion criteria**

- Women with multiple pregnancies.
- Women with seizures attributed to a diagnosis other than eclampsia such as; central nervous system infections, a history of seizures or epilepsy, medications and/or illicit drug use.
- Women unable to provide informed consent

## Data collection and management

Once eligible participants are identified, they will be provided with a patient information leaflet and invited to partake in the study. If written informed consent is provided:

1. Participant is enrolled in the study
2. Data will be collected by a trained research nurse or clinician (trained in interview techniques and the use of REDCap)
3. Data will be collected by directly asking the participant a series of standardised structured interview questions and review of medical charts
4. Participants will be followed until postpartum discharge, with maternal and neonatal outcomes recorded.
5. Using an iPad, all data will be entered into the secure online database REDCap, with each site having an individual database, with appropriate local translations.
6. All data will be accessible via the lead site and chief investigator.

## Outcome measures

The primary outcome is the presence or absence of a clinical signature of imminent eclampsia, unique both from women with preeclampsia and healthy normotensive pregnant women. To determine this, we have designed a standardised questionnaire collecting the following information:

| Maternal characteristics | Obstetric/booking information | Signs/symptoms | Eclampsia | Outcome |
| --- | --- | --- | --- | --- |
| First name | Gestation at booking | Highest systolic BP | Date of onset | Delivery date |
| Last name | Date at booking | Highest diastolic BP | Location of onset | Gestation at delivery |
| Maternal age | Estimated due date | Highest proteinuria | Prior magnesium sulphate | Indication for delivery |
| Address | How was due date estimated | Lowest platelet count |  | Mode of delivery |
| Race | Height | Highest AST |  | Live born |
| Marital status | Weight | Lowest haemoglobin |  | Sex |
|  | Antenatal care | Edema |  | Birthweight |
|  | Gravidity/parity | Tendon reflexes |  | Apgar at 5 minutes |
|  | Previous viable pregnancy outcome | Headaches, severity and onset |  | Neonatal outcome |
|  | Systolic BP at booking | Visual disturbances/type and onset |  | Number of days in hospital (maternal) |
|  | Diastolic BP at booking | Epigastric pain |  | Adverse maternal outcome |
|  | Proteinuria at booking | Tightness in chest |  |  |
|  | Antihypertensive medication | Shortness of breath |  |  |
|  | Tobacco/alcohol/drug use | Focal neurological deficit |  |  |
|  | Diabetes | Nausea/vomiting |  |  |
|  | Chronic hypertension | Confusion |  |  |
|  | Cardiovascular disease | Twitching/jerking of extremities |  |  |
|  | Anaemia | Mind state |  |  |
|  | HIV status | Concentration |  |  |
|  | Respiratory disease | Speech |  |  |
|  | Inflammatory bowel disease | Hearing |  |  |
|  | Autoimmune disease | Changes in moods |  |  |
|  | Malaria | Dizziness |  |  |
|  | Renal disease | Weakness or paralysis |  |  |
|  | Neurological disease | Jitters/nervousness |  |  |
|  | Medication use |  |  |  |

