## Background

Eclampsia is a serious pregnancy complication that occurs when a pregnant woman - or new mother - experiences seizures associated with hypertension. These seizures pose a major risk to the life and the health of mothers and unborn babies. Signs or symptoms of severe preeclampsia are not always present or easy to recognise before a woman develops eclampsia. This is why it can be difficult to tell which women are likely to develop eclampsia before the first seizure occurs. If we can identify the features that are most common and unique to eclampsia, these could be used to develop a tool to help identify the women displaying signs or symptoms that occur prior to the onset of eclamptic seizures. This would mean that treatment to prevent seizures could be targeted to the right women and quickly administered before they become extremely unwell with this life-threatening complication.

The development of a tool to predict eclampsia in high-resource settings (such as Australia) has been largely hampered by the extremely low prevalence of this complication1. This makes it challenging for researchers in this setting to conduct impactful studies and obtain reliable and detailed information about the characteristic features of eclampsia. However, rates of eclampsia, like many other complications, are far greater in low to middle income countries (LMICs; including South Africa, Pakistan and the Solomon Islands), with an estimated 16-69 cases of eclampsia per 10,000 livebirths2,3. Thus, research conducted in LMIC settings allow for the prospective recruitment of a relatively large cohort of women with eclampsia. They are a useful target population to prospectively characterise the signs and symptoms preceding the disease. *Such characterisation may yield a unique clinical signature for eclampsia and the development of a predictive algorithm.*

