## Study design

This is a multicentre prospective observational study in which women will be consecutively recruited, with four centres currently recruiting:

- Tygerberg Hospital, Cape Town South Africa
- Fatima Memorial Hospital, Lahore, Pakistan
- Jinnah Hospital, Lahore, Pakistan

Clinical signs and symptoms experienced by the women prior to enrolment in this study will be centrally recorded via the online database Research Electronic Data Capture (REDCap) and used to identify the presence or absence of a unique clinical signature able to predict imminent eclampsia.

Chief investigators at each site will be responsible for training and familiarising recruiting and study staff with the use of the REDCap and online data collection via the supplied iPad.

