## Recruitment

Women presenting with eclampsia, preeclampsia or healthy pregnancies will be eligible to participate, with recruitment aiming to enrol *all women with eclampsia or preeclampsia at each site*.

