## Statistical analysis

Data will be collected and analysed in clinically relevant categories with I2 or Mann-Whitney U tests used to detect difference between groups. We will compare data from women with eclampsia to those with i) preeclampsia and ii) normotensive pregnancies, to determine the unique signs and symptoms that precede eclampsia. Odds ratios will be used to determine strength of association for clinical characteristics significantly associated with eclampsia. We will also attempt to create a predictive score for eclampsia.

1. Knight M. Eclampsia in the United Kingdom 2005. *BJOG: An International Journal of Obstetrics & Gynaecology.* 2007;114(9):1072-1078.

3. Frias AE, Jr., Belfort MA. Post Magpie: how should we be managing severe preeclampsia? *Current opinion in obstetrics & gynecology.* 2003;15(6):489-495.

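### A primary result of absence would rest on failure to reject alone, because odds ratios are planned only for significant signs and no interval is mentioned

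*Protocol*

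**What the plan says.** Under Outcome measures the primary outcome has two values: "The primary outcome is the presence or absence of a clinical signature of imminent eclampsia", with the signature having to be unique against both preeclampsia and healthy normotensive pregnancy. Study design has the same pair: the recorded signs and symptoms are "used to identify the presence or absence of a unique clinical signature able to predict imminent eclampsia". No third, inconclusive result is provided for.

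The Statistical analysis section names a rank test and a test printed as I2 (read here as chi-square, the symbol probably lost in text extraction), these being "tests used to detect difference between groups". The comparisons and their purpose are set out in a sentence that begins: "We will compare data from women with eclampsia to those with i) preeclampsia and ii) normotensive pregnancies, to determine the unique signs and symptoms that". Effect estimates come after the tests: "Odds ratios will be used to determine strength of association for clinical characteristics significantly associated with eclampsia".

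The protocol gives no significance level, confidence interval, smallest relevant association, target number of women or definition of absence.

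**The concern.** A test that does not reject shows only that the data were insufficient to detect a difference. It does not show that the difference is small. To tell these apart a reader needs the estimate and its interval, and the odds-ratio sentence provides an estimate only where the test has rejected. Where the question is whether a sign has no association or was merely too infrequent to test well, the plan offers no odds ratio to look at.

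This is the opposite error to false positives from testing many signs. It bears most on infrequent items. The questionnaire lists focal neurological deficit, twitching or jerking, and weakness or paralysis; if these prove uncommon, they are the most exposed. The study is meant to support a tool for recognising women at risk of a seizure, so a bare report of absence could be taken as evidence that such signs are not warnings.

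**Working it through.** **No figure to reproduce.** The protocol states no sample size, power, significance level or effect size. It aims to enrol every woman with eclampsia or preeclampsia at the sites, and its Background gives only a rate, "with an estimated 16-69 cases of eclampsia per 10,000 livebirths". From that rate, 100 cases need between 100 / 0.0069 = about 14,500 and 100 / 0.0016 = 62,500 livebirths. Modest case numbers are plausible but not certain. Everything below is illustration under assumptions.

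**Assumptions.** Eclampsia/preeclampsia group sizes 50/200, 100/400 and 200/800; two-sided 0.05; uncorrected chi-square; comparison with preeclampsia only. For a sign with frequency q in preeclampsia and true odds ratio R, the frequency in eclampsia is p = Rq / (1 − q + Rq). For example, q = 5% and R = 2 gives p = 0.10 / 1.05 = 9.5%; q = 5% and R = 5 gives p = 0.25 / 1.20 = 20.8%.

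**Miss rate.** This is 1 − P(chi-square > 3.84 with the excess in eclampsia), obtained by exact enumeration of both binomial counts.

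| Frequency in preeclampsia | Odds ratio | Frequency in eclampsia | 50/200 | 100/400 | 200/800 |
| --- | --- | --- | --- | --- | --- |
| 5% | 2 | 9.5% | 74% | 58% | 35% |
| 5% | 3 | 13.6% | 44% | 18% | 2% |
| 5% | 5 | 20.8% | 9% | 1% | 0% |
| 2% | 3 | 5.8% | 67% | 47% | 23% |
| 2% | 5 | 9.3% | 35% | 11% | 1% |
| 10% | 2 | 18.2% | 63% | 39% | 13% |

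**A very rare sign with equal groups.** At 5% against 1% (odds ratio 5.2), exact power is 15%, 37% and 86% with 50, 100 and 300 women per group, so the miss rate is 85%, 63% and 14%. The answer turns on the unstated numbers.

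**What an interval adds.** Take 5 of 100 with eclampsia against 1 of 100 in a comparator:
- Chi-square = 200 × (5×99 − 1×95)² / (100 × 100 × 6 × 194) = 2.75, p = 0.097. As planned, no odds ratio is given.
- Odds ratio = (5 × 99) / (95 × 1) = 5.21. Standard error of the log = √(1/5 + 1/95 + 1/1 + 1/99) = 1.105. The 95% interval is exp(1.651 ± 1.96 × 1.105) = 0.60 to 45.4.

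The interval excludes neither no association nor a very strong one, and a reader given only a non-significant result would not know it. More generally, for the 5% sign with true odds ratio 2, among the data sets in which it is missed, the upper 95% limit (Wald, 0.5 added to each cell) exceeds 2 in 99%, 98% and 95% at the three sizes. The intervals would nearly always show that the result is inconclusive.

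**Second comparison.** Uniqueness also requires a difference from normotensive women, so the miss rate for both comparisons together is at least as high as for one. The increase may be negligible: with a 5% sign, odds ratio 3, 100/400 and 400 controls at an assumed 1% frequency, it stays at 18%.

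**The case against.** The strongest case against is that the protocol nowhere writes the rule being criticised. It does not say that a non-significant sign is ruled out, and it states no 0.05 threshold. That is correct. That absence would follow from non-significance is an inference from two sections read together. It stands because no other route to the conclusion is given.

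Three stronger readings are tempting, and the text does not support them:
- *Rare but specific signs are likely to be wrongly ruled out.* Likely cannot be defended without a sample size. In the table, 5% signs with odds ratio 5 are nearly always found, and an odds ratio of 2 on a 5% sign (9.5% against 5%) is hardly a unique feature.
- *Missing one sign produces a finding of absence.* Presence or absence refers to the signature as a whole. The miss rates are per sign and are not the probability of a false absence.
- *Missed signs drop out of the predictive score.* The protocol says only that a score will be attempted and gives no selection rule.

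It can also be said that group frequencies will surely be shown under Aim 1, and that intervals are often left to an analysis plan, which is not available here. Frequencies probably will appear, so a non-significant sign would not be wholly undescribed. But the protocol is not silent on effect estimates: it ties the odds ratio to significance, and a later plan would have to widen that sentence.

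**Conclusion.** The point holds in a limited form. As written, the protocol permits a primary conclusion of absence while limiting odds ratios to significant characteristics and mentioning no interval, so absence would have no effect estimate or bound behind it. That part rests on the text and needs no assumption about numbers.

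The size of the risk does depend on assumptions: group sizes, sign frequencies and the 0.05 level are all supplied here. Within the range shown, moderate associations in uncommon signs may often be missed and strong ones mostly are not, except when the sign is very rare and the groups small. The change is worth making because it corrects a stated rule at almost no cost and alters what a negative primary result can claim.

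**What to change.** In Statistical analysis, replace the odds-ratio sentence with: *Odds ratios with 95% confidence intervals, against preeclampsia and against normotensive pregnancy, will be reported for every listed sign and symptom, whether or not significant.*

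In Outcome measures, add: *If no signature is found, the result will be reported as no signature identified, read together with these intervals, and not as evidence of absence.* Align the matching phrase in Study design.

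No fixed exclusion margin is needed. A rule such as an upper limit below 2 would be a debatable choice: at the three assumed sizes, a 5% sign with no association at all would meet it only 2%, 17% and 46% of the time.

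The cost is two wording changes, a longer results table and a less definite negative conclusion. No additional data are required.

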**Inclusion criteria**

*Eclampsia:*

- Diagnosed as new onset generalized tonic colonic seizures or coma in pregnant women or women who have recently given birth.
- Singleton pregnancies.
- All gestational ages, including post-partum eclampsia
- Enrolment to the study must occur within 7 days of an eclamptic episode
- Women must be coherent and able to provide informed consent prior to enrolment

*Preeclampsia:*

- Diagnosed as new onset of hypertension (>140 mmHg systolic or > 90 mmHg diastolic) after the 20th week of gestation and the coexistence of one or more of the following new onset conditions:
  - Proteinuria
  - Other maternal organ evolvement:
    - renal insufficiency (creatinine >90 umol/L)
    - liver involvement (elevated transaminases and/or severe right upper quadrant or epigastric pain)
    - neurological complications
    - haematological complications (thrombocytopenia, DIC, haemolysis)
  - Uteroplacental dysfunction
    - Fetal growth restriction
- All gestations >20 weeks
- Singleton pregnancies
- Have not experience an eclamptic episode

*Normotensive controls:*

- Healthy normotensive pregnant woman recruited from women seeking maternity services during the same or similar time period
- Matched by closest gestation and parity.

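### The primary outcome's contrast with healthy controls includes chart-only signs for which the protocol provides no standard measurement in controls

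*Protocol*

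**What the plan says.** The protocol's Outcome measures section defines the primary outcome as a clinical signature that is "unique both from women with preeclampsia and healthy normotensive pregnant women". Aim 2 and the Statistical analysis section carry this down to individual features: characteristics of women with eclampsia are compared with each of the two other groups to find the distinguishing signs and symptoms, and odds ratios then measure the strength of association.

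The signs column of the data table mixes two kinds of item. Most are symptoms that any woman can report. Others need a laboratory or an examiner, such as "Lowest platelet count", highest AST and "Tendon reflexes". The laboratory items are recorded as extreme values.

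The Data collection and management section gives the source for all groups: "directly asking the participant a series of standardised structured interview questions and review of medical charts". It sets no blood test, urine test, examination or measurement schedule. Follow-up to postpartum discharge is for maternal and neonatal outcomes.

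The Inclusion criteria describe the control group as "Healthy normotensive pregnant woman recruited from women seeking maternity services during the same or similar time period", matched on gestation and parity. No laboratory test or examination is tied to control status beyond the BP reading that the word normotensive implies. The data table also collects BP and "Proteinuria at booking".

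**The concern.** An odds ratio between two groups is interpretable when the feature is looked for in the same way in both. Interview symptoms meet that condition, because the same structured questions can be put to every woman. AST, platelet count and tendon reflexes do not clearly meet it. Under the stated sources they come from the chart, and a chart holds them only if someone in routine care had occasion to measure them.

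Ascertainment may also differ by group. The preeclampsia criteria name creatinine, transaminases, thrombocytopenia and proteinuria among the qualifying conditions, so some work-up is linked to that diagnosis. The control definition has no counterpart.

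At stake is which laboratory and examination signs appear to distinguish eclampsia from healthy pregnancy, and how strongly. An analysis plan can set rules for missing values, but it cannot supply measurements that were never made.

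**Working it through.** The protocol states no sample size, error rate, power or feature prevalence, so it has no figure to reproduce. The structural point comes from the text. The arithmetic below shows only possible size, and every input is an assumption.

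**1. Which items are affected**

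- Interview symptoms (headache, visual disturbance, epigastric pain, mood and similar): obtainable from every woman. Not affected.
- BP: collected at booking and needed to call a woman normotensive. Available in every woman.
- Proteinuria: a booking value is collected, so it is a weaker example.
- AST, platelet count, tendon reflexes: no stated occasion for measurement in controls. These are the clear cases.

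**2. Selective testing of controls**

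Assume that all eclampsia cases are tested and 30% are abnormal. Let *p* be the true prevalence in controls, and let *a* and *b* be the probabilities that an abnormal and a normal control is tested. Among tested controls:

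observed prevalence = *pa* / (*pa* + (1 − *p*)*b*)

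The observed control odds are the true odds times *a*/*b*, so observed OR = true OR × *b*/*a*.

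With *p* = 3%, true OR = (0.30/0.70)/(0.03/0.97) = 13.9.

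| a | b | Share of controls tested | Observed prevalence | Observed OR |
|---|---|---|---|---|
| 0.3 | 0.3 | 30.0% | 3.0% | 13.9 |
| 0.6 | 0.3 | 30.9% | 5.8% | 6.9 |
| 0.6 | 0.1 | 11.5% | 15.7% | 2.3 |
| 0.9 | 0.1 | 12.4% | 21.8% | 1.5 |

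Varying *p* under the 0.6/0.1 pattern: at 1% the OR goes from 42.4 to 7.1, and at 5% from 8.1 to 1.4. When *a* = *b* there is no bias and only precision is lost.

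**3. Unrecorded values counted as normal**

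Same case, *p* = 3%, *a* = 0.6: apparent control prevalence = 0.03 × 0.6 = 1.8%. OR = (0.30/0.70)/(0.018/0.982) = 23.4, above the true 13.9. The same charts give 2.3 or 23.4 depending on how a blank is treated.

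**4. Extremes and number of readings**

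Suppose there is no true difference, and a single reading crosses an abnormal cut-off 5% of the time. The chance that the worst of *k* independent readings crosses it is 1 − 0.95^*k*:

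- *k* = 1: 5%
- *k* = 3: 14%
- *k* = 8: 34%

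Cases read eight times against controls read once would show OR = (0.337/0.663)/(0.05/0.95), about 9.6, with no real effect. Readings on one woman are correlated, so the true inflation would be smaller. The direction is opposite to that in step 2.

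**5. Net direction**

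Step 2 pulls the odds ratio towards no difference, and steps 3 and 4 push it away. The protocol does not say who is tested, how often, or how blanks are coded, so neither the sign nor the size of the net bias can be derived from it.

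**The case against.** The strongest reply is that the protocol shows no bias and says only that measurement follows routine care. Several parts of that reply stand.

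- A reader might infer that controls with a recorded AST or platelet count were tested because something was suspected. The protocol does not say why or how often controls are tested. If testing is routine or unrelated to status, only precision suffers. A high rate of abnormal values also sits awkwardly with a group selected as healthy.
- A reader might infer that every feature must be distinct from both groups and is dropped if the control contrast fails. The outcome concerns a signature, which may be a combination, and no such dropping rule is written. What stands is that Aim 2 and the Statistical analysis section identify features through both comparisons, so a distorted control contrast can still influence which ones are picked.
- A reader might infer that the preeclampsia contrast is free of the problem. It is not: hypertension with proteinuria alone qualifies as preeclampsia, so AST, platelets and reflexes need not be recorded there, and the eclampsia criteria require none of them either.
- The database response codes are not shown, so it cannot be said that a code for an unmeasured item is lacking.

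It can also be said that the research nurse or clinician could test reflexes at interview. Nothing forbids this, but nothing provides for it: the stated training covers interviewing and the database, and the Study design section concerns signs and symptoms before enrolment. That part of the reply does not close the gap.

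**Conclusion.** The point holds in a limited form. The primary outcome includes a contrast with healthy women, and for AST, platelet count, tendon reflexes and other signs not routinely recorded, the protocol provides no standard measurement in controls. For those items the odds ratio against controls may reflect who was tested and how often, as well as the condition itself.

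Under the assumed testing patterns with 3% control prevalence, a true odds ratio of 13.9 could be observed anywhere from 13.9 down to 1.5. Counting blanks as normal, or measuring cases more often, would move it upwards. These figures rest on assumed prevalences, assumed testing probabilities, complete testing of cases in step 2, and independent readings in step 4. They show that the effect can be large, not that it will be.

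The documents do not support a claim that the bias runs in a known direction, that controls are tested on suspicion, or that the whole signature is compromised. Interview symptoms are unaffected and BP is available in every woman.

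**What to change.** In the Outcome measures and Statistical analysis sections:

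1. Base the formal uniqueness contrast with normotensive controls on items obtained from every woman: the interview symptoms and BP. Highest BP is also an extreme value, so it should be read with the number of readings in mind.
2. For chart-only laboratory and examination items, show control values descriptively, with the number and share tested in each of the three groups.
3. Interpret the eclampsia versus preeclampsia contrast for those items beside the same tested counts, since complete measurement is not guaranteed there either.
4. State that an unrecorded item is not analysed as absent or normal. If the site databases do not already separate unmeasured from normal, add that response.

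No new tests or examinations are needed. The scientific cost is that the study makes no claim of uniqueness against healthy women for the chart-only items. The practical cost is a wording change and, if a response code is missing, one change per item in each site's database and its translations. Recruitment is already under way, so records entered before such a change may need a chart check to tell unmeasured from normal.

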## Aims

**Aim 1:** To characterize the clinical signs and symptoms that occur prior to the onset of eclampsia in a prospectively collected cohort.

**Aim 2:** Compare these characteristics to women with preeclampsia and healthy normal pregnancies to identify which features represent a unique clinical signature for eclampsia to form a simple predictive algorithm.

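### Six or seven of the 25 candidate signs need a staff measurement; when the seizure starts outside hospital these will often be taken after it or selectively missing, yet all cases are pooled

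*Protocol*

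**What the plan says.** The first aim in the Protocol (Aims) is "To characterize the clinical signs and symptoms that occur prior to the onset of eclampsia in a prospectively collected cohort". The Outcome measures section makes the primary outcome a signature of imminent eclampsia.

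The signs column of the table in Outcome measures mixes two kinds of entry. Some come from staff, for example "Highest systolic BP", "Highest proteinuria", "Lowest platelet count" and "Tendon reflexes". Most of the others, such as headache, visual disturbance or dizziness, can be obtained by interview. The eclampsia column of the same table lists the date of onset and "Location of onset".

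The Study design section has signs recorded for the period before enrolment. The Inclusion criteria allow a woman with eclampsia to be enrolled up to 7 days after an episode, and do not restrict where the seizure began. The Data collection and management section names interview and chart review as the sources.

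The Statistical analysis section states: "We will compare data from women with eclampsia to those with i) preeclampsia and ii) normotensive pregnancies, to determine the unique signs and symptoms". It plans odds ratios and an attempt at a predictive score. Location of onset has no stated role there.

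**The concern.** A symptom can be asked about wherever the seizure began. A blood pressure, platelet count or reflex examination shortly before the seizure exists only if the woman was already in contact with staff. The protocol collects the place of onset, so it allows for this to vary between cases.

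Two results are possible for a woman with onset outside hospital and no recent measurement:

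- Her highest or lowest value comes from admission after the seizure. It then cannot count as a sign that preceded the seizure.
- Only pre-seizure values are used and hers is missing. The measured signs then describe a different set of cases from the interview symptoms, although both feed one signature and one score.

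At stake is what the primary outcome describes. A measured feature could enter the signature because of what followed the seizure, or be reported for all eclampsia when it was observed only in women under care.

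**Working it through.** The protocol states no sample size, power or share of out-of-hospital onset, so there is no figure of its own to reproduce. The check is a row count, a comparison of sections, and an availability calculation under assumed values.

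**1. Row count (Outcome measures, signs column).**

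| Rows counted as needing staff | Count | Share of 25 |
| --- | --- | --- |
| Systolic BP, diastolic BP, proteinuria, platelets, AST, haemoglobin | 6 | 24% |
| plus tendon reflexes | 7 | 28% |
| plus "Focal neurological deficit" (self-report or examination) | 8 | 32% |
| plus edema (self-report or examination) | 9 | 36% |

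Six is the firm count and seven a fair one. The last two rows are borderline.

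**2. Time window.**

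- Target (Aims): before the onset of eclampsia.
- Recording rule (Study design): before enrolment.
- Gap between the two (Inclusion criteria): up to 7 days.
- Limit on the highest and lowest values (Outcome measures): none stated.

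As written, values obtained during those days can be the recorded extreme. This holds for any case, but for a woman with onset outside hospital and no earlier measurement they are the only values available.

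**3. Availability if only pre-seizure values are kept.** Let f be the share of seizures starting outside hospital, and a the share of those women with a usable earlier measurement, for example from antenatal care. Assume every in-hospital onset has one. Both f and a are assumptions.

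- Share of cases with a pre-seizure value = 1 − f + f·a
- Share of those values that come from outside onsets = f·a / (1 − f + f·a)

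| f | a | Cases with a value | Of these, outside onset |
| --- | --- | --- | --- |
| 20% | 0 | 80% | 0% |
| 20% | 30% | 86% | 7% |
| 20% | 60% | 92% | 13% |
| 40% | 0 | 60% | 0% |
| 40% | 30% | 72% | 17% |
| 40% | 60% | 84% | 29% |
| 60% | 0 | 40% | 0% |
| 60% | 30% | 58% | 31% |
| 60% | 60% | 76% | 47% |

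For f = 40% and a = 30%: 1 − 0.40 + 0.40 × 0.30 = 0.72, and 0.12 / 0.72 = 17%.

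Across these assumptions the measured signs would be available in 40% to 92% of cases. In every row with a below 1, outside onsets are under-represented among the values: at f = 40% and a = 30% they are 40% of cases but 17% of values. This is a calculation of availability, not an estimate of bias.

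**The case against.** The strongest reply has four parts.

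- **Onset outside hospital does not rule out an earlier measurement.** This stands. The protocol uses chart review and collects antenatal care and booking values for blood pressure and proteinuria. A reader might infer that such women can have no pre-seizure value, so that the measured signs rest only on women already in hospital. That would be true only at a = 0, and only if a pre-seizure limit applied, which the text does not impose. What these women will often lack is a value close to onset, and that is the value that matters for imminent eclampsia.
- **Missing-data rules and subgroup splits commonly sit in a statistical analysis plan.** This also stands, and the absence of such a rule here is no finding. The fault in this document is that the aim is pre-onset while the recording window runs to enrolment, with no limit on the extremes.
- **The direction of bias is unknown.** This stands. A reader might infer that odds ratios against preeclampsia are inflated because raised blood pressure brings women into care. That requires severe signs to be less common in out-of-hospital cases. If they are more common there, the bias reverses; if equally common, there is none from this source. The protocol supports none of these.
- **Preeclampsia comparators are defined by measured hypertension, so they are in care too.** Comparing them with in-care cases is like with like. This stands as support for the restricted analysis, provided the result is labelled for that population. It does not justify pooling all cases.

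**Conclusion.** The point holds in this form. Six or seven of the 25 candidate signs depend on staff measurement, and women whose seizure starts outside hospital will often lack such a value close before onset. With the recording window and pooled comparison as written, their measured signs are either post-seizure values or selectively missing. Either way, the measured part of the signature does not describe signs before onset in the same cases as the symptom part.

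The affected share of the candidate list is 24% to 28%, or up to 36% if both borderline rows are counted. The number of women affected and the direction and size of any bias cannot be computed from the protocol. The conclusion rests on two assumptions: that some seizures start outside hospital, which collecting the location suggests, and that not all of those women have a recent chart measurement.

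**What to change.** Make these changes, using chart review and fields that the protocol already plans:

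1. Date each measured value from the chart, and use only values dated before the first seizure for the signature. The date of onset is already collected. Values from the same day need their order relative to the seizure taken from the chart.
2. Estimate the odds ratios for interview symptoms, and a symptom-only score, in all cases.
3. Estimate the measured signs, and any score that contains them, only in cases with a pre-seizure measurement, against women with preeclampsia. Label these results as applying to women under care.
4. Report availability of each measured sign, and the results, by location of onset.
5. Treat an unmeasured sign as missing, never as absent or normal.
6. State which list the borderline entries (edema, focal neurological deficit) belong to.

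The cost is fewer cases and wider intervals for the measured signs, a change to the analysis wording, and the chart work needed to date the values, including for women already entered.
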